#### Evaluation of outcome measures

Table 4 shows the data to be collected from patients, GPs and practices for comparability of outcome measures between randomised groups, along with methods of analysis. Analysis will be of observed data only (no statistical methods for addressing missing outcome data, such as multiple imputation, will be used). However, the study will report on reasons for missing outcome data. Any between-group differences, indicating bias, will be evaluated. These evaluations will inform the methods of analysis of both dependent and explanatory outcome variables in the future trial, as well as a review of cost and resource implications. Examples of potential reasons for missing data include loss to follow-up, participants’ completion of questionnaires but non-attendance at the Index consultation, participants attending the consultation but not providing data on questionnaires, data lost or unavailable for other reasons, participants no longer able to experience post-consultation outcomes for example because they have died.

**Table 4 Tab4:** Evaluation of outcome measure processes

Data	Timing of data collection	Source of data	Type and total possible number of participants providing data	Type of data	Method of analysis
**Baseline**					
Practice characteristics (list size, location, deprivation)	Prior to randomisation	Practice and Association of Public Health Observatories website	6 practices	Categorical, nominal/ordinal.	Frequencies, to report data descriptively. Logistic hierarchical modelling to estimate between group differences^a^ (random effect on cluster, adjustment for practice location).
Patient age, gender, ethnicity, self-reported health status	Prior to index consultation	Pre-consultation postal questionnaire	180 patients	Categorical, nominal/ordinal.	Frequencies, to report data descriptively. Logistic hierarchical modelling to estimate between group differences (random effect on cluster, adjustment for practice location).
Patient deprivation data from patient postcodes	Following return of patient pre-consultation questionnaires and consent forms	Practice records mapped to the Index of Multiple Deprivation	180 patients	Continuous (IMD scale)	Mean and standard deviation, to report data descriptively. Linear hierarchical modelling to estimate between group differences^a^ (random effect on cluster, adjustment for practice location).
GP age, gender, ethnicity, time since qualification	Prior to index consultation	GP practices and General Medical Council GP registry	18 GPs	Categorical, nominal/ordinal	Frequencies, to report data descriptively. Logistic hierarchical modelling to estimate between group differences^a^ (random effect on cluster, adjustment for practice location).
Patients’ preferences for involvement in decision-making.	Prior to index consultation	Patient pre-consultation postal questionnaire	180 patients (90 per arm)	Ordinal (6 point Likert scale).	Frequencies, to report data descriptively. Logistic hierarchical modelling to estimate between group differences^a^ (random effect on cluster, adjustment for practice location).
**Clinical outcomes**					
Putative primary outcome					
Ratings of shared decision-making during the consultation from an observer perspective.	During data analysis	Assessment of video’d consultations by two trained researchers using the OPTION(5) score ([18] [19];)	18 GPs, 180 patients (9 GPs and 90 patients per arm)	Continuous (OPTION score 0-100%)	Mean and standard deviation, to report data descriptively. Linear hierarchical modelling to estimate between group differences* (random effect on cluster, adjustment for practice location).
Additional outcomes					
Patient-reported rating of involvement in decision-making about their healthcare	Immediately following the index consultation	Patient post-consultation questionnaire—using collaboRATE score ([18] [19];)	180 patients (90 per arm)	Continuous (collaboRATE score 0–100%)	Mean and standard deviation, to report data descriptively. Linear hierarchical modelling to estimate between group differences^a^ (random effect on cluster, adjustment for practice location). Patient and GP scores compared using logistic regression modelling (patient scores as outcome, GP scores as explanatory variable).
Patient-reported rating of feeling satisfied with the healthcare received	Immediately following the index consultation	Patient post-consultation questionnaire	180 patients (90 per arm)	Categorical, ordinal (3 point Likert scale)	Frequencies, to report data descriptively. Logistic hierarchical modelling to estimate between group differences^a^ (random effect on cluster, adjustment for practice location).
Patient-reported rating of having trust in the GP they saw				Categorical, ordinal (3 point Likert scale)	Frequencies, to report data descriptively. Logistic hierarchical modelling to estimate between group differences^a^ (random effect on cluster, adjustment for practice location).
Patient-reported rating of enablement				Discrete (PEI score 0–12)	Frequencies, to report data descriptively. Logistic hierarchical modelling to estimate between group differences^a^ (random effect on cluster, adjustment for practice location).
GP-reported rating of their involvement of the patient in decision-making about their healthcare	Immediately following the index consultation, after confirming patient consent for each aspect of data collection.	GP questionnaire using adapted collaboRATE ([18] [19];)	18 GPs (9 per arm)	Continuous (collaboRATE score 0-100%)	Mean and standard deviation, to report data descriptively. Linear hierarchical modelling to estimate between group differences^a^ (random effect on cluster, adjustment for practice location). Patient and GP scores compared using logistic regression modelling (patient scores as outcome, GP scores as explanatory variable).
Patient contacts in a 28-day period following the index consultation, including the nature of contact with the GP surgery, the hospital admissions, A&E attendances. If patient moved away within 28 days (i.e. lost to follow up)	Approximately 12 weeks after index consultation (to allow time for contacts to be recorded in the notes)	Case note review by two researchers	180 patients, (90 per arm)	Count	Median and range, to report data descriptively. Poisson hierarchical modelling to estimate between group differences^a^ (random effect on cluster, adjustment for practice location).
Deaths within a seven day period following the index consultation; death within 28 days (i.e. did not have full study follow-up).	Approximately 12 weeks after index consultation (to allow time for contacts to be recorded in the notes)	Case note review by two researchers	180 patients, (90 per arm)	Count	Median and range, to report data descriptively. Poisson hierarchical modelling to estimate between group differences^a^ (random effect on cluster, adjustment for practice location).
Documented decision outcomes from the index consultation, e.g. starting/stopping/changing medication, referrals and investigations	Approximately 12 weeks after index consultation (to allow time for contacts to be recorded in the notes)	Case note review by two researchers	180 patients, (90 per arm)	Binary (yes/no) variables for each type of change	Frequencies, to report data descriptively. Logistic hierarchical modelling to estimate between group differences^a^ (random effect on cluster, adjustment for practice location).
Process evaluation					
Participant experiences of the intervention, participants experiences of the study	Following receipt of participant post-consultation questionnaires and consent forms	Interviews with the participants from practices assigned to the intervention	9 GPs, 15 patients	Audio-recordings for qualitative analysis	Both deductive and inductive approaches to thematic analysis

^a^Between group differences will be reported using the appropriate outcome metric with 95% confidence intervals; no p-values will be reported in this feasibility study

Using an ‘intention to treat’ approach, participants will be analysed according to their randomised allocation irrespective of intervention actually received. However, all participants will be considered adherent by definition of the protocol. There is no mechanism by which participants in the control group could receive the intervention.

An intra-cluster correlation coefficient (ICC) will be calculated within each arm (intervention and control) for academic purposes; however, this will not be used to calculate a sample size for the future definitive trial; an estimated ICC, calculated from a large relevant routine dataset, will instead be sought [40].

The appropriateness of the outcome measures for use in a future, definitive trial of the intervention will be evaluated. The consistency with which certain outcome measures (e.g. OPTION(5), CollaboRATE, and those items taken from the GPPS survey) perform with the study population, when compared with previous performance in existing literature, will be reviewed. Findings will also be considered in the context of the internal consistency of performance of these measures within the participant sample. Consideration will be given as to whether the outcome measures chosen are sensitive to the effects of the intervention in the context of older people with multimorbidity in primary care, or whether there is a need for development of new measures.

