## Background

It is estimated that by 2032, there will be over 13.5 million patients in the UK aged 65 years and over, an increase of 50% when compared with 9 million in 2012 [36]. The prevalence of multimorbidity (more than one long-term health condition) increases with age [1]; 58% in people over 60 years compared with 14% in those under 40 years [30, 42, 43]. In developed countries, the prevalence of multimorbidity is also higher in females, among those with lower socioeconomic status (SES) and in minority ethnic groups [11, 45]. In those with lower SES, it is more common for mental and physical illness to co-exist. In addition, patients’ experiences of multimorbidity are affected by psychosocial and behavioural factors and larger health inequalities have been observed in vulnerable groups [39].

Consequences of ageing with multimorbidity include functional decline with poor quality of life and high healthcare costs [1, 26, 32]. The Department of Health [15] reported that older patients (those aged 65 and above) consult increasingly frequently (12–14 times/year in 2008/2009 vs. 6–7 times in 1995). Healthcare practitioners are often ‘medicalising’ the care of older people, diagnosing and treating each condition separately with new medication for example, and there are increasing rates of polypharmacy and new diagnoses [16].

There is evidence that involvement in healthcare decision-making is valued by older patients with multimorbidity [4, 9]. It is a means of effectively sharing the burden of treatment and enabling a holistic approach to clinical care [48]. Despite older patients typically expressing high levels of satisfaction with the care that they receive [7], they have been shown to be less frequently involved in decision-making when compared with younger, healthier patients [49], and there is a lack of recent evidence in this area. Therefore, whilst this patient group are often in receipt of ‘good-quality care’, there are concerns that this care is not currently meeting the complex needs of older patients with multimorbidity [48]. In addition, there is some evidence of an association between a lack of involvement and health inequalities for this patient group, for example, reduced rates of referral for postmenopausal bleeding and for hip pain [17, 28, 46].

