### Randomisation and blinding

The study will use a cluster randomised design. Clusters will be defined at practice level, with practices randomised 1:1 to usual care or to the intervention (90 patients per arm) following recruitment. Block randomisation will be stratified by site; two practices in inner city Plymouth, two practices from Exeter and two from rural Devon.

Randomisation will be conducted by an independent statistician who is blinded to the identity of practices. Blinding of the research team to outcome assessment will not be possible due to resource availability. Blinding of participants is unlikely to be achievable as participants in the intervention arm are likely to be aware that they are receiving more than standard ‘usual care’.

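### The Poisson model fixed for 28-day patient contacts leaves no room for variation between patients, so its 95% interval is too narrow if contacts are overdispersed

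*Protocol article*

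**What the plan says.** Table 4 of the protocol article defines the outcome as "Patient contacts in a 28-day period following the index consultation, including the nature of contact with the GP surgery, the hospital admissions, A&E attendances". It is classed as a count, described by median and range, and compared between arms by "Poisson hierarchical modelling to estimate between group differences", with a random effect for the cluster and location as an adjustment term. Under Randomisation and blinding the cluster is the practice: "Clusters will be defined at practice level, with practices randomised 1:1 to usual care or to the intervention (90 patients per arm) following recruitment". That section also gives three locations with two practices each: "Block randomisation will be stratified by site; two practices in inner city Plymouth, two practices from Exeter and two from rural Devon". The footnote to Table 4 sets the form of the result: "Between group differences will be reported using the appropriate outcome metric with 95% confidence intervals; no p-values will be reported in this feasibility study".

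The article names no dispersion parameter, patient-level random effect, negative binomial alternative or robust variance for this outcome. It gives no variance for contacts.

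**The concern.** Given practice, location and arm, a Poisson model assumes that all patients share one contact rate, so that variance equals mean. The patients here have two or more long-term conditions drawn from a broad list, and the row covers surgery contacts, admissions and A&E attendances. Unequal rates between patients make the variance exceed the mean. The direction of that departure is predictable; its size is not known from the protocol.

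The model is named together with its variance structure, so this is a choice that the text makes and not a detail it leaves open. With p-values ruled out, the 95% interval is the only inferential output for this outcome. An interval that is too narrow could make a chance difference in re-attendance look like a response to the intervention when outcome measures for the main trial are being weighed.

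**Working it through.** The protocol states no precision or coverage figure for this outcome, so there is none to reproduce. The benchmark is the nominal 95%.

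**Inputs from the protocol.** Six practices, three locations, one practice per arm in each location. There are 30 patients per practice if all 180 take part, or 180 × ½ ÷ 6 = 15 if half are recruited (Sampling). The only contact rate is in the Background, where patients aged 65 and over "consult increasingly frequently (12–14 times/year in 2008/2009": 12 × 28/365 = 0.92 and 14 × 28/365 = 1.07, so about 1 per 28 days.

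**Assumptions not in the protocol.** Variance-to-mean ratio φ of 1 to 3; between-practice SD of the log rate of 0 or 0.15; maximum likelihood with a Wald z interval; a mean of 2.0 as a sensitivity case. With gamma-distributed patient rates, φ = 1 + mean × CV². At mean 1, φ = 1.5, 2 and 3 therefore correspond to patient rates with a coefficient of variation of √0.5 = 0.71, 1.0 and √2 = 1.41.

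**Analytic check, Poisson without a practice effect.** The true SD of the log rate ratio is √φ times the model's standard error. With 45 patients per arm, mean 1 and φ = 2, the model SE is √(2/45) = 0.21 and the true SD is √(2 × 2/45) = 0.30. Coverage = 2Φ(1.96/√φ) − 1, which is 89% at φ = 1.5, 83% at φ = 2 and 74% at φ = 3.

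**Simulation of the stated model** (no true effect, 1000 runs per cell, mean 1.0). Entries are % coverage with 30 / 15 patients per practice. NB is a negative binomial model with the same practice random effect and location terms.

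| φ | Poisson, practice SD 0 | Poisson, practice SD 0.15 | NB, practice SD 0 | NB, practice SD 0.15 |
|---|---|---|---|---|
| 1 | 94.2 / 94.8 | 89.7 / 91.9 | 94.4 / 95.1 | 89.8 / 92.1 |
| 1.5 | 89.9 / 89.6 | 85.1 / 86.8 | 94.4 / 93.6 | 91.5 / 91.8 |
| 2 | 84.9 / 84.6 | 82.2 / 83.1 | 94.2 / 93.1 | 91.8 / 93.1 |
| 3 | 77.9 / 79.4 | 76.4 / 78.0 | 95.3 / 93.8 | 93.5 / 93.4 |

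**How much the practice effect absorbs.** At φ = 3 with no true practice variation (300 runs per cell), coverage was 79% with the practice effect and 75–76% without it. Six practices less four fixed effects (intercept, arm, two location terms) leave 2 degrees of freedom for the practice variance. It was estimated at zero in roughly 45–85% of the overdispersed runs.

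**How much is due to having six clusters.** At φ = 1 and practice SD 0.15 there is no overdispersion, yet the Poisson model covers only 90–92%. At mean 2.0 and practice SD 0.15 (600 runs per cell, φ = 1.5 to 3), the Poisson model covers 72–83% and NB only 86–92%. A paired cluster-level comparison, using the three within-location log ratios on t with 2 degrees of freedom, covered 94–97% in every cell with φ from 1.5 to 3, at both means.

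**The case against.** The strongest reply is that excess patient-level variance also inflates the spread of practice totals, so a practice random effect should pick it up. In principle that is right, and some absorption is visible in the simulation. With 2 degrees of freedom for the practice variance it is weak, so the concern stands.

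A second reply is that the size is assumed. That stands. The protocol gives no variance for contacts, and its rate of 12–14 a year is for consultations among older patients generally. Table 4 also does not say that the types of contact are summed. If admissions or A&E attendances were modelled separately, their means would be lower and, for the same spread in patient rates, φ would be nearer 1.

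A third reply is that little depends on the result. This is an additional outcome, the trial is unpowered and does no hypothesis testing, and none of the progression criteria refers to it. That also stands and limits the severity.

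Three stronger readings go further than the document allows:
- A reader might infer that the planned intervals cover some definite figure, such as 80–85%. That needs φ near 2, which the protocol does not supply.
- A reader might infer that a negative binomial model by itself restores 95%. It does not when practices differ, because six clusters with a z interval under-cover even without overdispersion.
- A reader might infer that patients who die or move away are analysed as if observed for the full 28 days. The text does not say so. Table 4 identifies such patients ("If patient moved away within 28 days (i.e. lost to follow up"), and the protocol expects little loss.

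**Conclusion.** The concern holds in conditional form. The model fixed in Table 4 allows no patient-level variance above the mean, and the practice effect makes up little of the gap. With a mean near 1 contact per 28 days, a variance 1.5 to 3 times the mean, and a between-practice log-SD of 0 or 0.15, the nominal 95% interval covers about 90% down to 76%. If the counts are not overdispersed, this fault disappears and only the shortfall from having six clusters remains. The variance ratio, the between-practice SD and the Wald interval are assumptions. Severity is minor.

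**What to change.** In Table 4, replace the Poisson model for 28-day contacts with a negative binomial model, or with Poisson plus a patient-level random effect or a dispersion-scaled variance. Keep the practice random effect and the location adjustment. Of these, the negative binomial version with the practice effect is the one checked above.

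Because six clusters with a z interval still under-cover, either state in the report that the interval is approximate, or use a small-sample t interval.

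The change affects the analysis wording only and needs no new data. The cost is a wider interval when counts are overdispersed; when they are not, the dispersion change alone has almost no effect on coverage (first row of the table). A t interval is wider still: on 2 degrees of freedom the multiplier is 4.303 instead of 1.96, or 4.303/1.96 = 2.2 times the width for the same standard error.

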### Sampling

Six GP practices will be recruited from rural Devon and from each of the cities of Exeter and Plymouth, UK. A minimum practice size of 3000 patients will ensure sufficient numbers of eligible participants. (It is anticipated that there will be approximately 800 older patients with multimorbidity in an average 8000 patient practice [1]). Table 1 shows the participant inclusion and exclusion criteria. An average of three (total = 18 GPs), and at least 2, GPs per practice will be recruited. Patients aged 65 and above with known multimorbidity, defined as the presence of two or more long-term conditions (as specified in Table 1), will be approached.

**Table 1 Tab1:** Participant inclusion and exclusion criteria

Participant type	Inclusion criteria	Exclusion criteria
GPs	Only permanent GPs (partners and salaried) to avoid loss to follow-up.	Locum (sessional) GPs Trainee GPs (GPs will not be excluded based on less than full time working)
Patients	Patients aged 65 and above with known multimorbidity The condition should be one of^a^: angina or long-term heart problem; arthritis or long-term joint problem; asthma or long-term chest problem; blindness or severe visual impairment; cancer in the last five years; deafness or severe hearing impairment; diabetes; epilepsy; high blood pressure; kidney or liver disease; long-term back problem; long-term mental health problem; long-term neurological problem.	Temporary residents and vulnerable patients e.g. those recently bereaved, those with severe mental illness, severe cognitive impairment, end stage disease, communication difficulties e.g. physical impairment caused by a stroke as opposed to language barriers, a learning disability, or those unable to complete questionnaires or interviews for any other reason. (A minimum time for a condition to be ‘long-term’ will not be specified)

^a^This list was adapted from the English National General Practice Patient Survey [10]. Where dyads of conditions occur within the same organ system, e.g. anxiety and depression, these will only be counted once e.g. mental health problem

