Patient participants will be identified using an automated practice database search strategy designed by the research team. The practice administrative team will use this ‘flag’ to identify ten consecutive potential participants with pre-booked consultations with each of the three recruited GPs. Random sampling of participants is not required as the clinical presentations, and therefore the nature of the decision-making between consecutive consultations, is expected to be random. A total of 180 (minimum 120) potential patients will be identified across 6 practices, with the aim of recruiting at least half.

The sample size is sufficient to compare between-group differences in quantitative feasibility objectives such as recruitment rates and data collection procedures including the completeness of participant questionnaires. This sample size also allows the estimation of standard deviations for the clinical outcome measures being tested. In addition, it is sufficient to obtain a purposively selected sub-sample of participants for process evaluation interviews, to achieve the qualitative feasibility objectives.

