#### Evaluation of resources and capacity to manage the study and implement the intervention

A cost-effectiveness framework for a subsequent definitive trial will be developed by identifying, measuring and valuing the resources used to deliver the intervention. For example, the time required to identify ten consecutive eligible patients per GP will contribute to informing the time required for intervention delivery in the future trial. Data collection processes will be tested with consideration of estimations of the size and range of cost components, along with reporting of the resource use categories prone to missing data. For example, the acceptability of administering questionnaires will be analysed by reporting missing values and presenting mean scores and 95% confidence intervals.

Patient safety data will be described numerically in both intervention and control practices (no hypothesis testing), e.g. hospital admissions, attendances at A&E and deaths within 7 days of the index consultation.

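### Table 4 summarises deaths by a median and a hierarchical Poisson model, and fits a hierarchical logistic model to six practice-level values; neither is likely to give a usable result

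*Protocol article*

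**What the plan says.** Table 4 (protocol article, Evaluation of outcome measures) has a row under Clinical outcomes for "Deaths within a seven day period following the index consultation; death within 28 days (i.e. did not have full study follow-up". The row gives 180 patients (90 per arm), types the data as a count, and sets the analysis as "Median and range, to report data descriptively. Poisson hierarchical modelling to estimate between group differences", with a random effect on cluster and adjustment for practice location.

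Under Baseline, the row "Practice characteristics (list size, location, deprivation" has six practices as its source. It prescribes frequencies and also a hierarchical logistic model for the between-group difference, with "random effect on cluster, adjustment for practice location". Under Randomisation and blinding, the practice is the cluster, allocation is 1:1, and randomisation is stratified by site with two practices in each of three sites.

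Footnote a to Table 4 says that differences come with 95% confidence intervals and without p-values.

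The section Evaluation of resources and capacity to manage the study and implement the intervention says: "Patient safety data will be described numerically in both intervention and control practices (no hypothesis testing". It names hospital admissions, A&E attendances and deaths within 7 days as examples.

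**The concern.** The deaths row has the same summary and model as the row above it, 28-day contacts. Contacts are a true count per patient; death is 0 or 1. The next row, on documented decisions, is also binary and is summarised by frequencies, so the table already contains a suitable form. A median cannot show how many patients died, and a Poisson contrast needs events in both arms, which short follow-up of a small sample is unlikely to provide.

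In the practice row, the unit of observation is the cluster itself, so nothing varies within a cluster to support a random effect.

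At stake is a published commitment to report these differences with 95% confidence intervals. The team would have to report failed or meaningless fits, or depart from the plan.

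**Working it through.** **Sample size.** Inputs from Sampling: "Six GP practices will be recruited from rural Devon and from each of the cities of Exeter and Plymouth, UK"; "An average of three (total = 18 GPs), and at least 2, GPs per practice will be recruited"; "identify ten consecutive potential participants with pre-booked consultations with each of the three recruited GPs". Then 6 × 3 × 10 = 180 patients and 3 × 3 × 10 = 90 per arm, which reproduces Table 4. The stated aim is to recruit at least half of those identified, so 45 per arm is the lower case.

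**Median and range of deaths.** Each value is 0 or 1. The median exceeds 0 only if at least half of an arm dies: 45 of 90, or 23 of 45. Even at an assumed risk of 5%, the probability of that is below 10⁻¹⁶. The range can only be 0–0 or, with any death, 0–1. This result needs no realistic mortality figure.

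**Poisson contrast for deaths.** The document gives no mortality rate, so annual mortality r is an assumption, taken as 2% to 10%.

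- Risk over d days: p = 1 − (1 − r)^(d/365).
- Probability that an arm of n has no deaths: P0 = (1 − p)^n.
- Probability that at least one arm has none: 1 − (1 − P0)².

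Worked case, n = 90, r = 10%, d = 28: p = 0.00805, P0 = 0.483, and 1 − 0.517² = 0.733.

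| n per arm | Days | Expected deaths, both arms | P(no deaths at all) | P(at least one arm with none) |
|---|---|---|---|---|
| 90 | 7 | 0.07 to 0.36 | 0.93 to 0.70 | 0.999 to 0.972 |
| 90 | 28 | 0.28 to 1.45 | 0.76 to 0.23 | 0.983 to 0.733 |
| 45 | 7 | 0.04 to 0.18 | 0.97 to 0.83 | >0.999 to 0.992 |
| 45 | 28 | 0.14 to 0.72 | 0.87 to 0.48 | 0.995 to 0.907 |

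(Each range runs from r = 2% to r = 10%.) With no deaths in one arm the rate ratio is 0 or infinite, and with none in either it is undefined. In each case there is no finite log rate ratio. The calculation treats patients as independent; variation in risk between practices would raise P0, so it does not weaken the result. The exclusion of end-stage disease also makes deaths rarer.

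**Practice characteristics.** There are six observations, one per cluster. The fixed part has an intercept, an arm term and two location terms: 4 parameters for 6 observations, before any variance. A logistic model has no free residual variance, and with a single observation per cluster there is no replication from which to estimate a cluster variance.

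Taking the random effect out does not rescue the model. Stratified 1:1 allocation puts one practice per arm in each site. For a binary characteristic there are 2⁶ = 64 outcome patterns. All four coefficients are finite only if the two practices differ in every site (2³ = 8 patterns) and do not all differ in the same direction (2 patterns): 8 − 2 = 6 of 64. The arm coefficient alone is finite if at least one site differs in each direction: 64 − 27 − 27 + 8 = 18 of 64.

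For location itself, the outcome is also the adjustment variable, and the stratification already balances it by design.

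**Table 4 against the text.** The text describes 7-day deaths and does no testing. Table 4 estimates a between-group difference for the same deaths, with an interval and no p-value. The text does not name 28-day deaths, and practice characteristics are not safety data.

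**The case against.** The strongest reply is that nothing important turns on these rows. This is a feasibility trial without a power calculation or hypothesis tests. The progression criteria concern recruitment and data collection, and the putative primary outcome is the OPTION(5) score. Table 4 already gives frequencies for the six practices, and a failed fit would be plain to the analyst. All of this stands, and it limits the point to a minor one.

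A reader might infer that Table 4 contradicts the safety plan. The documents do not support that. The text excludes testing and footnote a excludes p-values, so description and interval estimation can coexist. What remains is an inconsistency about 7-day deaths only.

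A reader might also infer that the number of deaths would be hidden. It would not: the text commits to a numerical description of 7-day deaths by arm, the flow of participants and attrition will be recorded, and death is named among possible reasons for missing outcome data. Nor does the protocol rank deaths as its main safety comparison.

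The remedy has limits too. Exact binomial intervals ignore clustering within practices, and listing very rare deaths by practice could make individuals recognisable. Neither should be required.

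The reply does not make the prescribed summaries work. Reading the count as deaths per practice does not help either: the row's unit is patients, and an arm without deaths still gives no finite log rate ratio.

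**Conclusion.** The point holds as a minor fault in what Table 4 prescribes. The median and range of deaths are uninformative for any plausible data. The Poisson contrast very probably has no finite estimate: with 90 per arm, at least one arm has no deaths with probability 97% or more at 7 days and 73% or more at 28 days. Those percentages rest on an assumed annual mortality of 2–10% and on independence between patients. The fault in the practice-level model is structural and needs no assumption about event rates: one value per cluster, four fixed terms for six observations, and location as both an outcome and its own adjustment variable.

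**What to change.** In Table 4:

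- **Deaths at 7 and 28 days:** report n/N (%) by arm, with no median and no model. Exact 95% confidence intervals are optional, with a note that they ignore clustering. They stay reportable with no events: the upper limit is 1 − 0.025^(1/n), which is 4.0% for 0/90 and 7.9% for 0/45.
- **Practice characteristics:** describe the six practices by arm, with no model.
- **Consistency:** align the deaths row with the descriptive statement in the section on resources and capacity. The same section also names admissions and A&E attendances, which sit in the Poisson-modelled contacts row, so it is worth stating there whether they are described only or also modelled.

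The cost is a change of wording in Table 4 and less analysis work. Data collection, sample size and conduct are unaffected.
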